#### Sample size {14}

We will recruit 200 working-age adults (18–65 years of age) suffering from one or several of the following disorders: depression (ICD-10: F32 or F33), anxiety (ICD-10: F41), or exhaustion. The sample of participants will be randomised into four groups (50 + 50 + 50 + 50) of which two groups (*n* = 100) will receive vibroacoustic treatment (VAT) and two groups (*n* = 100) not whereas two groups (*n* = 100) will receive music listening (ML) and two groups (*n* = 100) not (see Table 2).

**Table 2 Tab2:** Factorial design

	VAT yes	VAT no	
ML yes	50	50	*n* = 100
ML no	50	50	*n* = 100
	*n* = 100	*n* = 100	

For each condition, the selected sample size provided a statistical power of 0.985 for detecting a medium standardised effect size of Cohen’s d = 0.5 in a mixed-model analysis [47], with a 2-tailed significance level of *p* < 0.05 and intra-participant correlation of ρ = 0.6. For the comparison between IIMT only vs waiting-list control, the selected sample size provided statistical power of 0.9 for detecting a medium effect size (d = 0.23) in a repeated measures t-test, with a 2-tailed significance level of *p* < 0.05. These high-power levels ensure a robust detection of clinically meaningful effects, even after accounting for potential participant dropouts, while reducing the likelihood of Type II errors. Also, the selected sample sizes also retain adequate power (> 0.8) to detect smaller effects (e.g., d = 0.2), thus providing sensitivity to subtle group differences.

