## Statistical methods

### Statistical methods for primary and secondary outcomes {20a}

All statistical tests will be two-tailed with a significance level of 5%, and no adjustments will be made for multiplicity. Primary and secondary outcome measures at baseline, post-intervention, and at the first and second follow-ups will be treated as continuous dependent variables.

For the IIMT group, which also serves as the waiting-list control, we will assess clinical improvement by comparing their progress during the intervention period with that observed during the waiting period prior to treatment. Specifically, we will perform paired samples t-tests for each outcome measure, comparing the change from baseline 2 (6 weeks; pre-intervention) to post-intervention (12 weeks) against the change from baseline 1 (0 weeks; no intervention) to baseline 2 (6 weeks). Prior to analysis, we will assess the normality of the difference scores to ensure the assumptions of the t-test are met. This comparison will help isolate the treatment effect from natural fluctuations over time.

Since the participants are randomised either to the waiting list plus plain IIMT group or to one of the other three arms (B, C, and D), comparisons between plain IIMT and the waiting list are based on within-subject analyses rather than fully randomised group contrasts. No direct comparisons between the waiting list group and arms B, C, and D will be performed.

To evaluate the effects of VAT and ML on these outcomes, repeated-measures linear mixed-effects models will be applied [50]. A key advantage of this design is its ability to retain participants with missing data, ensuring that all participants contribute to the analysis. Additionally, they can account for baseline group differences, to avoid overestimating the effect size of treatment. VAT and ML will be included as fixed effects, with a random intercept for each participant to account for the dependency of repeated measurements. To control for baseline differences across conditions, treatment terms will be omitted from the model, allowing the effects of VAT and ML to be estimated through their interactions with time. As an exploratory analysis, the models will be extended to include a VAT × ML interaction term to examine potential synergistic effects between the two interventions.

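### The stated power above 0.8 at d = 0.2 is wrong for differences between groups: at the plan's own correlation it is about 0.38 to 0.64 for a 100 v 100 factor contrast and 0.21 to 0.37 for 50 v 50

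*Protocol article*

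**What the plan says.** The section Sample size {14} of the protocol article makes three statements that bear on this point.

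- **Size and allocation.** "The sample of participants will be randomised into four groups (50 + 50 + 50 + 50", and for the factorial margins "two groups (*n* = 100) will receive vibroacoustic treatment (VAT) and two groups (*n* = 100) not"; the same split applies to music listening (ML).
- **Main power statement.** The sample gives "a statistical power of 0.985 for detecting a medium standardised effect size of Cohen’s d = 0.5 in a mixed-model analysis", "with a 2-tailed significance level of *p* < 0.05 and intra-participant correlation of ρ = 0.6".
- **Small effects.** The section then adds that "the selected sample sizes also retain adequate power (> 0.8) to detect smaller effects (e.g., d = 0.2", and concludes that subtle differences between groups can be detected. No model, correlation or number per side is restated for this sentence.

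The section Statistical methods for primary and secondary outcomes {20a} sets the significance level: "All statistical tests will be two-tailed with a significance level of 5%, and no adjustments will be made for multiplicity". It describes a linear mixed model with a random intercept, four measurement times (baseline and three later visits), and treatment main terms left out, so that VAT and ML act only through their interactions with time. It also defines an overall effect over time. Hypotheses 2 to 4 under Objectives {7} are worded as comparisons between single arms.

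**The concern.** With the design held fixed, power falls steeply as the effect shrinks. A sample with 0.985 power at d = 0.5 would not be expected to keep more than 0.8 at an effect two-fifths that size. The two statements stand in one paragraph and share one sample, so one can be tested against the other.

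VAT and ML are components of about 15 minutes placed before an active therapy that every arm receives, so small differences between arms are plausible. A reader who trusts the sentence would take a null result as good evidence against an effect of 0.2 SD. At the powers found below, the trial would miss such an effect in about 36% to 62% of repetitions for a factor contrast, and in about 63% to 79% for a contrast of single arms.

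**Working it through.** **Inputs**

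- Two-sided 5%, no multiplicity adjustment (sections {14} and {20a}): critical value 1.960.
- Correlation ρ = 0.6 between any two visits of one person (section {14}). A random-intercept model implies equal correlation at all spacings.
- Three post-baseline visits: post-intervention, 6 months and 12 months (sections {13} and {20a}).
- n = 100 per side for each factor (Table 2); n = 50 per side for single arms.
- d in units of the SD at one visit, with complete data.

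**Formulas**

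Power = Φ(d/SE − 1.960), with SE = √(2V/n). V is the variance factor of the analysed summary:

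- mean of three post-baseline visits: V = (1 + 2ρ)/3 = 2.2/3 = 0.7333
- the same mean in a baseline-constrained model: V = (1 + 2ρ)/3 − ρ² = 0.7333 − 0.36 = 0.3733

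**Step 1: reproduce the printed figure**

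Post-baseline mean, 100 v 100: SE = √(2 × 0.7333/100) = 0.1211. At d = 0.5, 0.5/0.1211 = 4.129, and Φ(4.129 − 1.960) = 0.985. This agrees with the protocol. The match does not identify the formula: the baseline-constrained model at 50 v 50 gives 0.9835, and the mean of all four visits at 100 v 100 gives 0.988.

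**Step 2: change only d, to 0.2**

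- Post-baseline mean, 100 v 100: 0.2/0.1211 = 1.651; Φ(−0.309) = 0.38.
- Baseline-constrained, 100 v 100: SE = √(2 × 0.3733/100) = 0.0864; 0.2/0.0864 = 2.315; Φ(0.355) = 0.64.
- Post-baseline mean, 50 v 50: SE = 0.1713; Φ(1.168 − 1.960) = 0.21.
- Baseline-constrained, 50 v 50: SE = 0.1222; Φ(1.637 − 1.960) = 0.37.

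Other direct contrasts at 100 v 100 give 0.29 (one post-baseline measure), 0.35 (change score), 0.42 (one post-baseline measure adjusted for baseline) and 0.49 (post-baseline mean minus baseline). None reaches 0.8.

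**Step 3: what 0.80 would require**

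- Number per side at d = 0.2: about 288 (post-baseline mean) or 147 (baseline-constrained).
- Smallest d at 100 v 100: (1.960 + 0.842) × SE = 2.802 × 0.1211 = 0.34, or 2.802 × 0.0864 = 0.24.
- Correlation at 100 v 100, baseline-constrained: V must fall to 100 × 0.2²/(2 × 2.802²) = 0.255. Solving (1 + 2ρ)/3 − ρ² = 0.255 gives ρ of about 0.77, against the stated 0.6.

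**The case against.** **No formula is printed.** The section cites a source for the mixed-model calculation and shows no equation, so neither set-up above can be called the plan's own formula. This stands, and it is why a range is given. The conclusion does not depend on the choice, since every direct contrast tried falls short of 0.8.

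**The lower figure ignores baseline.** The planned model leaves out the treatment main terms and so uses baseline information. This also stands: 0.64 is closer to the planned analysis than 0.38. Likewise, the 50 v 50 figures fit the wording of Hypotheses 2 to 4, whereas the factor effects in section {20a} are 100 v 100 contrasts.

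**Other calculations do exceed 0.8.** A repeated-measures group-by-time F-test with N = 200, ρ = 0.6 and f = 0.1 (from the usual f = d/2) gives 0.88 to 0.97 for two groups with two to four visits. A paired t-test on 200 people gives 0.804 at d = 0.2. Either could be the source of the sentence, but neither supports it. With two groups and two visits, the interaction effects are a quarter of the difference in change, so f = 0.1 means a difference of 0.4 SD, not 0.2: Φ(0.4/√(2 × 0.8/100) − 1.960) = Φ(1.202) = 0.885. The paired test is not a comparison of groups, and only the 50 people in Condition A have a waiting period; with n = 50 its power at d = 0.2 is 0.28.

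**Dropout.** A reader might infer that the section is also wrong to say that power holds "even after accounting for potential participant dropouts", since it gives no rate and no inflation. The documents do not support calling this an error. The clause can be read as saying that the margin absorbs losses, and at d = 0.5 it does: at an assumed 20% loss (80 v 80), power is 0.958 for the post-baseline mean and 0.999 for the baseline-constrained model.

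**The sentence sets nothing.** The sample size rests on d = 0.5, and the d = 0.2 sentence fixes no test or decision rule. That is true and limits the consequence, but a stated power that conflicts with the inputs beside it still needs correcting.

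**Conclusion.** The statement of more than 0.8 power at d = 0.2 for differences between groups is wrong as written. Power is about 0.64 (baseline-constrained, three visits averaged) or 0.38 (the inferred set-up that returns 0.985) for 100 v 100, and about 0.37 or 0.21 for 50 v 50. These figures assume ρ = 0.6 at all spacings, a two-sided 5% level, complete data, d in units of the SD at one visit, and an effect that is the same at all three visits.

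A reader might go on to infer that the trial is too small or that the 0.985 is false. Neither follows. The sample size is justified at d = 0.5, and that figure reproduces for the factor contrasts. The error is confined to the small-effect sentence and to how a null result would be read in its light.

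**What to change.** Delete the d = 0.2 sentence together with its conclusion about subtle group differences. Alternatively, replace it with the smallest effect detectable with 0.80 power at 100 v 100. The sponsor's statistician should recompute that effect from the formula actually used, naming the model, the visits averaged and the correlation. As a guide, it should come out near d = 0.24 for a baseline-constrained model averaged over three visits, or near d = 0.34 for the post-baseline mean. If single-arm comparisons are to be reported under Hypotheses 2 to 4, the corresponding 50 v 50 values are about 0.34 and 0.48.

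The cost is one reworded sentence and a less favourable figure. It needs no extra participants and no change to design or analysis. According to the Trial status section, recruitment is expected to run to the end of December 2028, so the correction can be made before results are known.

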#### Recruitment {15}

We will recruit 200 adults of working age who are 18–65 years of age, assessed with one or more of the following conditions: depression (ICD-10: F32 or F33), anxiety (ICD-10: F41), or exhaustion. Participants will be recruited from the middle-Finland area through newspaper announcements, media bulletin, flyers in psychiatric policlinics, health centres and public institutions (based on permissions), and social media. We will also inform local health care professionals about the study to enable recruitment through word of mouth.

The advertisements include the named contact people for the study. Those individuals interested in participating in the study may contact the named people by phone or email and enrol in the study if they wish. They are then informed about the study in more detail. Initially, the participants receive detailed information about the study, a research bulletin and a consent form, to make sure they have sufficient time to familiarise themselves with it before coming to the first appointment and making their final decision of participation. Screening will be conducted in the first assessment appointment as described earlier in this document. The participants have the opportunity to contact the research group at any time during the process and ask for additional information. The local health care professionals will be informed about the study. A separate permission for contacting the participant for further studies will be asked on the consent form.

## Assignment of interventions: allocation

### Sequence generation {16a}

The stratified randomisation will be performed using the random permuted block method.

The stratification factors will be age group, gender, employment status and health condition. An external biostatistician will create the program for randomisation. The randomisation table will be created using the SAS software, Version 9.4 of the SAS System for Windows (SAS Institute Inc., Cary, NC, USA). The table will be used to set up the randomisation module on REDCap, and REDCap will be used further for the randomisation. An external biostatistician does not have any contact to the study participants, and the sequence is kept concealed from those who do. Study data will be collected and managed using REDCap electronic data capture tools hosted at the University of Jyväskylä [48, 49]. REDCap (Research Electronic Data Capture) is a secure, web-based software platform designed to support data capture for research studies, providing 1) an intuitive interface for validated data capture; 2) audit trails for tracking data manipulation and export procedures; 3) automated export procedures for seamless data downloads to common statistical packages; and 4) procedures for data integration and interoperability with external sources.

### Concealment mechanism {16b}

Concealment is implemented by using central allocation through REDCap.

### Implementation {16c}

The participants will be enrolled by the assessors using the aforementioned screening tests. The randomisation will be carried out by the PI who will then inform another staff member about the participant’s allocation. The staff member will inform the next available therapist about the participant’s allocation, and the therapist contacts the participant. The participants are not informed about the presence of other conditions. For the waiting-list condition, the participants are invited for another screening (baseline 2) six weeks post the initial screening.

## Assignment of interventions: blinding

### Who will be blinded {17a}

The assessors will be blinded about the participants’ randomisation to different conditions throughout the assessment points.

### Procedure for unblinding if needed {17b}

Only the assessors are blinded and since they are external members not involved in the study in any other way, there will be no need for unblinding. In case of the participant revealing their allocation by chance, it will be recorded. However, the assessment will proceed as planned.

## Data collection and management

### Plans for assessment and collection of outcomes {18a}

The assessment is conducted in four different testing timepoints (except Condition A that has an extra testing timepoint before the intervention). All outcome measures are completed in all timepoints. The outcome data will be collected by the assessors using paper questionnaires. The assessors are healthcare professionals that have been trained to conduct the study protocol and procedures. The data will be stored in REDCap by researchers. REDCap software is suitable for collecting sensitive data. The software requires individual multi-factor authentication and only authorized staff that have a specific reason to handle the data will have access to it. The access to and collecting and storing of the data as well as access control will be monitored together with the University of Jyväskylä (JYU) IT services and information administration. In REDCap, the PI can assign different access rights to different research group members. The final complete data will be stored in a server that is subject to the JYU information security policy.

### Plans to promote participant retention and complete follow-up {18b}

The participants’ eligibility and ability to commit to the study is assessed at screening to ensure the fit to the protocol. The intervention is designed to meet the needs of the target group thus promoting participant retention and completing the intervention and the whole study. Participants are also encouraged to complete the study. The study will be implemented with high quality at all phases from recruitment to the last follow-up. All testing timepoints will be completed by the same assessor to ensure assessment coherence, and also to enhance participant retention. The participants can have information about their condition at all timepoints which will also promote their commitment to the study. No data will be collected after discontinuance of the study, however, all previously collected data will be included in the analysis.

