#### Criteria for discontinuing or modifying allocated interventions {11b}

The participants have the right to withdraw from the study at any point. The need to discontinue the intervention may arise, for example, due to the participant’s strongly weakened condition, physical limitations or changes in life situation. The possibility of modifying or discontinuing the intervention will be discussed between the assessor, supervisor, therapist and participant, considering participants’ wishes and any safety-related concerns. Therapists participate in group supervision, where possible modifications of the intervention or discontinuation of the intervention can be further discussed. The consulting psychiatrist may be contacted if needed.

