#### Participant timeline {13}

There are overall four to five testing timepoints in this study: during the recruitment of the participants (baseline), 6 weeks after the beginning of the intervention (post-intervention), 6 months after the beginning of the intervention (first follow-up) and 12 months after the beginning of the intervention (second follow-up). The waiting-list control group will have an additional testing timepoint (baseline 2) at 6 weeks after the initial baseline tests before starting the therapy. This will also act as a new baseline for the intervention.

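### The protocol claims assessor blinding throughout, but its visit schedule reveals Condition A to the MADRS rater, and the assessor also takes part in discussions of the allocated intervention

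*Protocol article*

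**What the plan says.** On blinding, Who will be blinded {17a} states: "The assessors will be blinded about the participants’ randomisation to different conditions throughout the assessment points". Procedure for unblinding if needed {17b} sees no need for an unblinding procedure, "since they are external members not involved in the study in any other way". Its only safeguard is to record a participant's chance disclosure and carry on with the assessment.

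Four other sections bear on that claim:

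- Plans to promote participant retention {18b}: "All testing timepoints will be completed by the same assessor to ensure assessment coherence".
- Participant timeline {13}: "The waiting-list control group will have an additional testing timepoint (baseline 2) at 6 weeks after the initial baseline tests". Plans for assessment {18a} confirms that the number of visits is the same for everyone "except Condition A that has an extra testing timepoint before the intervention".
- Criteria for discontinuing or modifying allocated interventions {11b}: the possibility of modifying or stopping the intervention "will be discussed between the assessor, supervisor, therapist and participant".
- Assessors also take consent {26a}, enrol participants {16c} and record changes in care at visits {11d}.

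The outcomes section describes MADRS as a clinician interview and a secondary outcome. CORE-OM, the primary outcome, is self-report.

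**The concern.** Blinding of a rater depends on what that rater sees. Here one person sees a participant at every visit, and one arm has a visit that no other arm has, so the schedule itself discloses that arm. Separately, someone who discusses with the therapist whether an allocated intervention should be changed is likely to learn what it is, and is not uninvolved in the sense that {17b} requires.

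What is at stake is the credibility of the one outcome that depends on the assessor's judgement. If a rater knows that a participant waited and then received plain IIMT, expectation can enter the MADRS score. Condition A is part of the reference level for both factors and is the only arm in the waiting-list comparison. As things stand, the trial report would claim blinding that its own protocol contradicts.

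**Working it through.** The protocol gives no figure to reproduce here. The check is a side-by-side reading followed by simple weights.

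**1. What the assessor sees.** Inputs are {13}, {18a}, {18b} and the week numbers in Statistical methods {20a}. I assume that therapy in B, C and D starts promptly after baseline.

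| Visit | Condition A | Conditions B, C, D |
|---|---|---|
| 1st | week 0 (baseline) | week 0 (baseline) |
| 2nd | week 6 (baseline 2, before therapy) | week 6 (post-intervention) |
| 3rd | week 12 (post-intervention) | 6 months after therapy start |
| 4th | 6 months after therapy start | 12 months after therapy start |
| 5th | 12 months after therapy start | none |

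The second visits fall at about the same time and use the same measures, so they could look alike if they were not labelled. The protocol does not provide for that, and Implementation {16c} treats baseline 2 as a further screening. The third visit cannot be mistaken: in B, C and D the third visit is the 6-month follow-up, so only an A participant comes back to the same assessor at 12 weeks. A late start of therapy in B, C or D makes their third visit later still and does not remove the difference.

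Hence A is recognisable at baseline 2 if that visit is labelled, and at the latest at week 12. A's post-intervention, 6-month and 12-month MADRS ratings are not blind. The schedule does not tell B, C and D apart.

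**2. What the assessor's role discloses.** {17b} says there is no other involvement, while {11b} makes the assessor a party to intervention discussions. Both cannot hold. Consent and enrolment also contradict the wording of {17b}, but they come before allocation and disclose nothing.

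**3. How many participants.** From Sample size {14}: A is 50/200 = 25% of the trial, 50/100 = 50% of the no-VAT margin and 50/100 = 50% of the no-ML margin.

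**4. Weight in the factorial effects.** For VAT, main effect = (C + D)/2 − (A + B)/2, so A has weight 1/2. The same holds for ML, (B + D)/2 − (A + C)/2.

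- A shift of x confined to A's post-baseline ratings moves each main effect by x/2 in absolute size: 0.5 point for x = 1.
- {13} makes baseline 2 a new baseline for A. If the model uses it and the same shift is already present there, part of the shift cancels. With a common baseline mean and the protocol's intra-participant correlation of 0.6, what remains is 0.5 × (1 − 0.6) × x = 0.2x: 0.2 point for x = 1.

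**5. Weight in the within-A test.** {20a} compares (post − baseline 2) with (baseline 2 − baseline 1). The contrast is post − 2 × baseline 2 + baseline 1.

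- A shift of b at baseline 2 alone contributes −2b.
- A shift of b at post alone contributes +b.
- An equal shift at both contributes b − 2b = −b.

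**The case against.** The strongest reply concerns scope. A reader might infer that all MADRS ratings are unblinded, but the documents do not support that. The schedule separates A from the rest and nothing more. The {11b} discussions are occasional, and {11b} does not say that the condition is named in them. Participants are not told that other conditions exist {16c}, which limits accidental disclosure. Someone who leaves the study contributes no later rating {18b}. All of this stands.

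A reader might also infer that the assessor certainly knows the arm from baseline 2 onward, or that blinding at that visit is impossible. Neither is established, because the week-6 visits could be presented alike and nothing says that the assessor is given the visit label. Nor does the protocol rank MADRS as its main depression measure.

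On size, x is hypothetical, and no direction or magnitude of rater bias can be drawn from the documents. One might count the full x against the contrasts of B with A and C with A. Hypotheses 2 and 3 name those comparisons, but {20a} plans factor effects over time, so the full-x figure belongs to no analysis specified there.

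Finally, using one assessor per participant is a legitimate choice for consistency. The problem is its combination with an arm-specific visit and a role in intervention discussions. The reply narrows the point, but it does not reconcile {17a} and {17b} with {11b}, {13}, {18a} and {18b}.

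**Conclusion.** The concern holds in a limited form. The blinding described in {17a} and {17b} is not a property of the design as written. For Condition A, 25% of participants, the rater can tell the arm by the 12-week visit at the latest, so A's post-intervention and follow-up MADRS ratings cannot be called blind. For B, C and D, blinding is lost only where an {11b} discussion discloses the allocation.

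The consequence is confined to a clinician-rated secondary outcome; CORE-OM is not directly exposed. The possible effect on each MADRS main effect is about x/2 for a shift confined to A's post-baseline ratings, and less if the baseline used for A carries the same shift. In the within-A test a shift at baseline 2 alone counts twice. These are weights, not predicted bias. The conclusion rests on one assessor per participant being applied as stated, and on no masking of visits beyond what the protocol describes. The point should be corrected, but it does not threaten the primary analysis.

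**What to change.** 1. Reconcile {11b} with {17b} so that the person who rates MADRS is not party to discussions that reveal allocation. Who else takes part is for the clinical team.
2. Restate {17a} and {17b} so that the claim matches the schedule: Condition A versus the rest cannot be assumed blind from baseline 2, and is not blind from A's 12-week visit at the latest.
3. Record every instance of unblinding by arm, including that from the schedule or from discussions and not only a participant's chance disclosure. Do not report MADRS as fully assessor-blinded.

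The cost is protocol wording, one item on the assessment record and some rearrangement of who attends the discussions. No visits or participants are added. Recruitment is expected to run to the end of December 2028, so later ratings can still benefit.

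Changing the rater at A's baseline 2 alone is not advised. A systematic rater difference r at that visit enters the within-A contrast as 2r in absolute size, and a random one adds four times its variance. A rater who saw the first baseline could still infer Condition A from the 12-week return.
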